### This Trial

Therefore, leveraging a unique academic-industry partnership, we propose a 20-week RCT (8-week intervention+12-week follow-up) to rigorously test the consumer-based app Calm to effectively deliver a meditation intervention to patients with chronic hematological cancer (N=276; 138 per group) as compared with a health education podcast control group. Calm was chosen for this study as our research team had rigorously tested the app among patients with chronic hematological cancer previously, and we have demonstrated its preliminary efficacy and preference among patients with chronic hematological cancer over another popular meditation app, Headspace [47]. This study aims to (1) test the efficacy of daily meditation (≥10 minutes per day) delivered via Calm compared with a health education podcast control group in improving the primary outcome of self-reported sleep disturbance, as well as secondary sleep outcomes, including sleep impairment and sleep efficiency; (2) test the efficacy of daily meditation (≥10 minutes per day) delivered via Calm compared with a health education podcast control group on inflammatory markers (TNF-α, IL-6, IL-8, and CRP), fatigue, and emotional distress (anxiety and depressive symptoms); and (3) explore free-living use during a 12-week follow-up period and sustained effects at 20 weeks from the baseline of Calm in patients with chronic hematological cancer.

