Participants will be allowed to choose the time of day when they meditate. Giving participants autonomy over choosing the time of day for meditation mirrors the way in which Calm’s paying subscribers use the app, thus yielding benefits (eg, ecological validity and participant satisfaction) that likely outweigh those of imposing strict controls over the timing of use, which could lead to lower adherence (eg, missed or truncated practice). Participation (meditations completed, time of day, length of time, and nonmeditative content used) will be tracked using the Calm app throughout the study and addressed in sensitivity analyses.

After completion of the 8-week study intervention period, the Calm intervention participants will no longer have to complete daily meditations but will continue to have access to the app for 12 additional weeks during the follow-up period. Participation in the Calm app will continue to be tracked during this time.

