To address the hypotheses regarding the intervention effects on inflammatory markers (TNF-α, IL-6, IL-8, and CRP), fatigue, anxiety, and depressive symptoms, we will estimate models parallel to those estimated for sleep measures, with week 8 outcome values predicted based on the arm, adjusting for corresponding baseline values on outcome measures and relevant background covariates.

To address the hypotheses regarding longer-term intervention effects at week 20, we will use analytic approaches parallel to those to assess differences in change at week 8, with outcomes being predicted from arm or dose (minutes spent meditating), adjusting for corresponding baseline outcome values and background covariates.

To address the hypotheses regarding associations between dose and sustained meditation use (number of weeks with ≥4 days of meditation use) and longer-term change in outcomes within only the Calm intervention arm, we will examine bivariate plots and estimate a variety of multivariable regression models (eg, polynomial linear regression, piecewise linear function, and generalized additive models) to understand the forms of the associations of dose and sustained use and change in outcomes.

If preliminary analyses indicate significant arm × baseline interactions, we will use (instead of an ANCOVA approach) a generalized linear mixed model approach in which a cross-level arm (Calm vs podcast) × time (eg, baseline vs week 8) interaction term is the focal effect for predicting repeated measurements of the outcome measure. This interaction term will capture between-arm differences in changes from baseline to week 8 (or week 20). Differences in change as a function of the intervention dose will be captured using dose × time interaction terms. Although the generalized linear mixed model approach generally does not provide as much statistical power as the ANCOVA approach, generalized linear mixed models (estimated using maximum likelihood) have the advantage of drawing on the strength of all available covariate and outcome data to produce unbiased parameter estimates and SEs in the presence of outcome data that are missing at random.

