Prior studies using meditation to reduce sleep disturbance in patients with cancer did not have follow-up periods beyond 12 weeks [53]. In the 2 meditation-based interventions conducted in patients with chronic hematological cancer, both were delivered for a very short period (ie, 5 sessions of 1 hour per week). No product could be used continually and accessed beyond study completion [58,59]. As most evidence-based apps are developed within the context of research studies and are not sustained at the end of the study [96], the scalability and viability of the widespread distribution of mobile app–based interventions in these studies are not possible. As Calm is consumer based, the intervention never truly *ends*. Calm is available and can be used whenever a patient desires or feels it is needed (eg, when they feel overwhelmed, fatigued, anxious, or lying down to go to sleep). The patient can choose when and how frequently Calm is used, increasing the likelihood that patients will use Calm to alleviate sleep disturbance in the long term. This study can uniquely measure and explore time and dose effects and will advance the evidence for a consumer-based meditation app that patients with chronic hematological cancer can use for symptom self-management in the long term. This research will contribute to broader public health efforts by providing researchers and clinicians with an evidence-based commercial product to improve sleep in the long term in an underserved and understudied population with cancer and a high incidence of sleep disturbance.

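### Week-20 outcomes are related to voluntary app use without separating weeks 9-20 from weeks 1-8 or conditioning on week-8 status, so the exploratory aim 3 use associations can be confounded in either direction

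*Protocol article*

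**What the plan says.** The third aim (Protocol article, This Trial) is to "explore free-living use during a 12-week follow-up period and sustained effects at 20 weeks from the baseline of Calm". Once the 8-week intervention ends, Calm participants "will no longer have to complete daily meditations but will continue to have access to the app for 12 additional weeks" (Intervention Group (Calm)), and their use continues to be tracked.

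Three passages in Analytic Approach deal with week-20 use:

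- Under longer-term intervention effects, the week-20 models have "outcomes being predicted from arm or dose (minutes spent meditating), adjusting for corresponding baseline outcome values and background covariates". The examples given earlier for background covariates, sleep medication dosage before the study and BMI, are pre-study characteristics.
- The next paragraph, on the Calm arm only, concerns "associations between dose and sustained meditation use (number of weeks with ≥4 days of meditation use) and longer-term change in outcomes". It names several regression forms and lists no covariates.
- If the mixed-model fallback is used, dose enters through a dose-by-time interaction.

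None of these is stated to condition on the week-8 outcome, and neither minutes nor the count of ≥4-day weeks is restricted to weeks 9-20. The sensitivity analyses cover time of day, nonmeditative content, changes in cancer regimen and new sleep disorder diagnoses. They do not cover week-8 response.

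**The concern.** Randomization does not protect a comparison of heavier with lighter users inside one arm. In weeks 1-8 everyone is asked to meditate daily and is prompted to do so. From week 9 each participant decides. That decision may well reflect how the participant is sleeping and feeling at week 8, and the week-8 score also predicts the week-20 score. Week-8 status would then be a common cause of exposure and outcome. Baseline adjustment cannot remove it, because it arises after baseline.

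The direction is open. If responders keep using the app, continued use looks beneficial even if it does nothing. If people who still sleep badly keep using it, continued use looks useless or harmful even if it helps. A measure summed over 20 weeks also mixes requested use with the free-living use that aim 3 asks about. At stake is the aim 3 statement on sustained use, not the primary result or the randomized week-20 comparison.

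**Working it through.** **Inputs from the article (Sample Size and Power).** Week-20 complete cases: 194, or 97 per arm. Pre-post correlation: 0.30. ISI SD: 6.0. Detectable dose-response effects at power 0.80: r² ≥ 0.039 (all cases) and r² ≥ 0.076 (Calm only).

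**Reproducing the article's figure.** F test of one coefficient at alpha 0.05, noncentrality n·r²/(1−r²):

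- n = 194, r² = 0.039: 194 × 0.039/0.961 = 7.87, power 0.797.
- n = 97, r² = 0.076: 97 × 0.076/0.924 = 7.98, power 0.798.

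Both figures reproduce at the week-20 sample sizes, so n = 97 is the right size for the Calm-only check.

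**Assumptions not in the article.** c is the correlation of week-8 with week-20 scores, taken as 0.30 (the article's only repeat-measure figure) and as 0.5-0.7. u is the correlation of weeks 9-20 use with the week-8 score given baseline, taken as 0.2-0.4 in either direction. Follow-up use has no effect on week 20.

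**Formula.** With standardized scores and both later scores correlated 0.30 with baseline, the spurious partial correlation of use with week 20, adjusting for baseline only, is

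ρ = u(c − 0.30²)/(1 − 0.30²) = u(c − 0.09)/0.91.

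The spurious slope in SD per SD of use is u(c − 0.09)/√0.91. The rejection rate is approximately P(|Z + δ| > 1.99), with Z standard normal and δ² = 97ρ²/(1−ρ²).

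| c | u | ρ | δ | Rejection rate |
|---|---|---|---|---|
| 0.30 | 0.2 | 0.2 × 0.21/0.91 = 0.046 | 0.46 | 0.07 |
| 0.30 | 0.4 | 0.4 × 0.21/0.91 = 0.092 | 0.91 | 0.14 |
| 0.5 | 0.2 | 0.2 × 0.41/0.91 = 0.090 | 0.89 | 0.14 |
| 0.6 | 0.3 | 0.3 × 0.51/0.91 = 0.168 | 1.68 | 0.38 |
| 0.7 | 0.4 | 0.4 × 0.61/0.91 = 0.268 | 2.74 | 0.77 |

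Simulation (at least 4,000 data sets per scenario) agrees: about 7%-15% at c = 0.30, about 14%-76% at c = 0.5-0.7, and 37%-38% at c = 0.6, u = 0.3. Changing the sign of u reverses the slope and leaves the rate about the same. With the week-8 score added, the rate returns to about 5% in every scenario (0.044-0.055).

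**Size of the spurious slope.** At c = 0.6, u = 0.3: 0.3 × 0.51/0.954 = 0.16 SD per SD of use, or 0.16 × 6 ≈ 1 ISI point. The largest spurious r² in the table is 0.268² = 0.072, just below the 0.076 that the article treats as detectable.

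**If the dose measure also includes early use.** Suppose early use unrelated to the week-8 score makes up half the dose variance. Then u is multiplied by √0.5 = 0.707. At c = 0.6, u = 0.3, ρ falls to 0.119 and the rate to about 21%-22%. Over c = 0.5-0.7 and u = 0.2-0.4 the rate is about 9%-47%.

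**The case against.** The strongest reply is that aim 3 is exploratory and the within-Calm paragraph speaks of associations. In the scenarios above, use and the week-20 score really are associated given baseline, so a rejection is an error only if the result is read as an effect of use. This is a fair limit on severity. It does not remove the point, because the article also places dose under longer-term intervention effects and powers what it calls dose-response effects.

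Four stronger readings are tempting, and the text does not support them:

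- A reader might infer that the article itself declares follow-up use to be symptom-driven. Comparison With Prior Work says only that Calm "can be used whenever a patient desires or feels it is needed (eg, when they feel overwhelmed, fatigued, anxious" and so on. That describes the availability of a consumer product, not a measured pattern in weeks 9-20. The argument needs only that use is voluntary.
- A reader might infer that baseline-only adjustment is fixed for the sustained-use models. That wording belongs to the preceding paragraph, and it adds background covariates. For the within-Calm models the adjustment set is not stated, and baseline-only is an inference.
- A reader might treat 14%-76% as the expected error rate. It needs a week 8-20 correlation above the only figure in the article, and a use-week-8 correlation for which the article has no source. The calculation also leaves out the planned Hommel adjustment.
- A reader might assume a week-8 value for every participant. It is scheduled for all, but the article anticipates up to 20% attrition by then.

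A further objection stands. Adjusting for week 8 would remove part of any benefit of early use, so it suits weeks 9-20 use only and must not be applied to cumulative dose.

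**Conclusion.** The point holds as a confounding risk in the exploratory use analyses. The stated week-20 dose model contains no post-baseline outcome value, the within-Calm models specify no adjustment, and the exposure window is open although aim 3 asks about the free-living period. The resulting associations can be false in either direction.

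The size is not known from the documents. It runs from a small inflation at a week 8-20 correlation of 0.30 to a severe one at 0.7 with use strongly tied to week-8 status. It shrinks when early use dilutes the dose measure. The calculation assumes linear relations, normal scores, 97 completers and no effect of follow-up use. Severity is minor to moderate: a cheap improvement to an exploratory aim.

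**What to change.** In Analytic Approach, for the Calm-only analyses:

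1. Define use separately for weeks 1-8 and weeks 9-20.
2. Relate the week-20 outcome to weeks 9-20 minutes and to the number of ≥4-day weeks in weeks 9-20, adjusting for the week-8 value of the same outcome, its baseline value and weeks 1-8 minutes.
3. Handle missing week-8 values with the planned multiple imputation.
4. Keep adjustment for baseline, without week 8, for the randomized arm comparison, for weeks 1-8 dose and for any cumulative-dose analysis. In the dose analyses the week-8 value may lie on the causal path from early use.
5. Report the results as exploratory associations.

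The cost is wording and two extra covariates in a model with about 97 participants. No new data are needed, since week-8 outcomes are scheduled and app use is tracked through both periods. The change removes only confounding through the measured week-8 outcome. Confounding that arises within weeks 9-20, and other reasons for continuing to use the app, will remain.

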### Control Group (Health Education Podcast)

Similar to the Calm intervention group, podcast group participants will listen to a minimum of 10 minutes per day of a health education podcast delivered via a mobile app for 8 weeks (Tables 1 and 2). A library of health education podcasts will be available on the app, with carefully chosen content that excludes any recommendations for sleep, meditation, or mindfulness-like principles or practice. Participants will be able to select the podcast based on title, time, or both in an effort to mirror the delivery of meditations in the Calm intervention group. Podcast group participants will also be encouraged to use other components of the podcast. Participation (podcasts completed, time of day, length of time, and components used) will be tracked on the app throughout the study period. After completion of the 8-week sham intervention period, the podcast group participants will no longer be asked to listen to daily podcasts but will continue to have access to the app for 12 additional weeks during the follow-up period. Participation in the podcast app will still be tracked during this period. Upon completion of the entire 20-week study period, podcast group participants will be given a discount code for 6 months of free access to the Calm app.

**Table 1 table1:** Calm and podcast group prescriptions.

Week	Calm intervention group	Podcast group^a^
Week 1: total 7 days	Daily introductory 10-minute meditation	Daily 10-minute health education podcasts
Weeks 2-4: total 21 days	Daily 10-minute exploration of mindfulness meditation	Daily 10-minute health education podcasts
Weeks 5-20: Full access	Full library of individual and series of 10-minute meditations	Full library of podcasts available

^a^Podcasts will be uploaded weekly, except during weeks 5-20 when the remaining full library will be uploaded.

**Table 2 table2:** Examples of Calm and podcast group prescriptions.

Group and examples			Minutes

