### Statistical Analysis

#### Sample Size and Power

All estimates presented here are conservatively based on a generalized linear mixed model analytic approach, in which the focal effect is an arm (Calm vs podcast) × time (baseline vs 8 or 20 weeks) interaction. A generalized linear mixed model approach affords lower power than the preferred analysis of covariance (ANCOVA) approach, which will be pursued if the model’s homogeneity of effect assumption is met (see the *Analytic Approach* section). Assuming a sample SD for ISI scores of 6.0 (derived from the literature on sleep disturbance among patients with cancer [81-85]) and Cronbach α=.05, a complete-case sample size of 28 (n=14 pee arm) would afford a power of 0.80 to detect a clinically meaningful between-arm (Calm vs podcast) differences in ISI scores of >7 points (ie, a standardized between-arm difference of Cohen *d*=1.33). However, anticipated effects on other sleep measures and measures of well-being are generally much more modest; accordingly, the study sample size was determined based on anticipated intervention effects on these outcomes rather than those on the ISI. In our previous work, we found moderate effects of meditation on self-reported psychological well-being (aim 2; Cohen *d*_s_=0.31-0.44), self-reported sleep disturbance assessed via the PROMIS Sleep Disturbance questionnaire (Cohen *d*=0.47), and inflammation biomarkers (Cohen *d*_s_=0.41-0.50) [39]. The meta-analysis by Duong et al [86] suggests somewhat stronger effects of mindfulness (standardized mean difference 0.50) and relaxation (standardized mean difference 0.94) interventions on fatigue. Assuming an effect size typical of those observed across these various outcomes (Cohen *d*=0.45), a conservative estimate of the pre-post correlation for outcome scores (*r*=0.30) and Cronbach α=0.05, a complete-case sample (at 8 weeks) of 220 (n=110 per arm) should afford a power of 0.80 to detect significant between-arm differences in secondary outcomes (and power >0.99 to detect a clinically meaningful difference in ISI scores). Anticipating up to 20% attrition at 8 weeks, we will enroll and randomize 276 participants (n=138 per arm). For aim 3, anticipating up to 30% attrition by week 20 (yielding 194 complete cases; n=97 per arm), tests of intervention effects should have power=0.80 to detect the effects of Cohen *d*≥0.48. Multivariable linear regression analyses of potential dose-response effects on outcomes will take two forms: (1) analysis of all available cases with a dose coded as 0 for the podcast group and (2) analysis using data from the Calm group only. These analyses should have a power of 0.80 to detect small (*r^2^*≥0.039) and moderate (*r^2^*≥0.076) linear dose-response effects.

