
#### Analytic Approach

For preliminary analyses, univariate and bivariate statistics and plots will be used to examine the distributions of and associations between study variables, identify potential multivariate outliers and influential cases, explore patterns of missingness, and check for systematic between-arm differences in baseline participant characteristics. Before addressing the study aims, we will estimate multivariable linear regression models predicting week 8 and week 20 values of each outcome from the main effects of the treatment arm (arm) and the corresponding baseline value of the outcome (baseline) and an arm × baseline interaction term. If the interaction is not significant, an ANCOVA-type approach (described in the following paragraphs) will be used. However, if this interaction is significant, a generalized linear mixed model approach will be used, with repeated measurements of outcomes treated as nested within the participants. Preliminary analyses will inform the choice of link function (eg, natural log) and error distributions (eg, negative binomial) or the transformation of outcome scores used in the primary analyses. R (version 4.1.2) will be used for all analyses and plots.

To assess intervention effects on sleep quality and sleep-related impairment, we will use multivariable linear regression models (following an ANCOVA-type approach), predicting week 8 values on the ISI and secondary sleep outcomes, including the PROMIS Sleep Disturbance questionnaire and Sleep-related Impairment Scale, and sleep efficiency measured via sleep diaries and actigraphy from the study arm (Calm v podcast), adjusting for corresponding baseline values and relevant background covariates (eg, prestudy sleep medication dosage and BMI). These analyses, which will follow a strict intent-to-treat approach, will be supplemented by parallel analyses in which week 8 outcome values will be predicted from dose (minutes of meditation use), with the dose coded as 0 for the podcast arm, while adjusting for baseline outcome measure values and background covariates. These supplemental analyses will address heterogeneity in intervention exposure without including highly collinear arm and dose terms in the same models.

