All preliminary analyses will be supplemented by analyses exploring the interactions between biological sex (male vs female) and the focal effect in each model (eg, sex × arm in ANCOVAs or sex × arm × time in generalized linear mixed models) to determine whether these effects differ by sex. Furthermore, we will conduct sensitivity analyses by examining associations between time of day (eg, proportion of meditation bouts occurring within 2 hours of bedtime) and the proportion of sessions using nonmeditative content and outcomes at 8 and 20 weeks, adjusting for baseline outcome values. As these variables will be highly collinear with the study arm because podcast users will not have any recorded in-app meditation use, sensitivity analyses gauging the potential impact of these variables will parallel the dose-response analyses described previously. Further sensitivity analyses will be conducted to assess the potential impact of (1) changes in the chronic hematological cancer treatment regimen and (2) sleep disorder diagnoses that occur after randomization. For these, analyses of intervention effects will be repeated, excluding data from individuals who experience either of these events, and the results will be compared with those from the full intent-to-treat sample. To maintain the type I error rates at a nominal Cronbach α=.05, we will use *P* values adjusted using the Hommel approach [87].

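### In its pooled form (podcast coded 0, no arm term), the session-timing and nonmeditative-content analysis measures the Calm-versus-podcast difference and should not be read as a timing or content effect

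*Protocol article*

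**What the plan says.** The Analytic Approach section describes sensitivity analyses "examining associations between time of day (eg, proportion of meditation bouts occurring within 2 hours of bedtime) and the proportion of sessions using nonmeditative content". Both features are to be related to week-8 and week-20 results, with the baseline value of the outcome as a covariate. The section gives a reason for the model chosen: "As these variables will be highly collinear with the study arm because podcast users will not have any recorded in-app meditation use". It concludes that "sensitivity analyses gauging the potential impact of these variables will parallel the dose-response analyses described previously".

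The dose-response analyses are described in two places. Sample Size and Power lists two forms. The first is "analysis of all available cases with a dose coded as 0 for the podcast group". The second, which leaves the podcast arm out, is "analysis using data from the Calm group only". Analytic Approach spells out the first, "with the dose coded as 0 for the podcast arm, while adjusting for baseline outcome measure values and background covariates", and says that this handles differences in use of the app "without including highly collinear arm and dose terms in the same models". It also plans Calm-only models of dose and sustained use for longer-term change.

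The article does not say which of the two forms the timing and content analyses will follow. For the podcast arm's own behaviour, the Control Group section states: "Participation (podcasts completed, time of day, length of time, and components used) will be tracked on the app throughout the study period".

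**The concern.** The question is whether, among people using Calm, session timing or extra content is related to outcome. The matching null hypothesis is no association within Calm.

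In the pooled form every podcast participant sits at 0, Calm participants sit at 0 or above, and no arm term separates the groups. The coefficient is then zero only if timing is irrelevant and Calm also has no effect. If Calm works, the slope from the podcast cluster at 0 up to the Calm participants is nonzero whatever the timing. This is separate from self-selection, because it happens even if timing is random within Calm.

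For minutes of meditation, 0 is a real value for a podcast user. For a proportion of meditation sessions it is not, because the denominator is zero.

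At stake is a secondary message. A trial in which Calm works could report that bedtime practice or nonmeditative content goes with better sleep when the model has only found the arm effect again. The Intervention Group section names sensitivity analyses as the way these self-chosen features will be addressed.

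**Working it through.** **Inputs from Sample Size and Power.** d=0.45 for planning; d=0.31 as the low end of the earlier effects; pre-post correlation r=0.30; alpha 0.05 (two-sided assumed); 110 complete cases per arm at week 8 and 97 at week 20.

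**Assumed, because the article does not give it.** The distribution of the proportion within Calm. Beta distributions with mean 0.10-0.50 and SD 0.15-0.35 were used.

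**1. The plan's own figures.** For a difference in change scores the variance is 2(1-0.30)=1.4, so n per arm = 2 × 1.4 × (1.960+0.842)² / 0.45² ≈ 109, against 110 stated. 220/0.80 = 275, against 276 stated. At week 20, 97 per arm and d=0.48 give power 0.803. The two detectable dose-response effects reproduce at the week-20 numbers: r²=0.039 with 194 participants gives power 0.797, and r²=0.076 with 97 gives 0.798. The article therefore plans for both the pooled and the Calm-only form.

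**2. What the pooled coefficient estimates.** Let P have mean m and SD s in Calm and be 0 in podcast, with 1:1 allocation. Then

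- covariance with arm = m/4, and variance of the zero-coded variable = m²/4 + s²/2;
- correlation with arm = m/√(m²+2s²);
- expected slope with no timing effect = −d·m/(m²+2s²).

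For a uniform proportion (m=0.5, s²=1/12) the correlation is 0.5/√0.4167 = 0.77 and the slope is −0.45 × 0.5/0.4167 = −0.54 SD per unit of proportion. The true value is 0. The simulated slope was also −0.54.

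**3. Approximate rejection rate.** The baseline-adjusted arm test has expected z = 0.45/√(1−0.09) × √(110/2) = 0.472 × 7.416 = 3.50. The pooled test has about that value times the correlation.

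- Uniform: 3.50 × 0.77 = 2.71, and Φ(2.71−1.96) ≈ 77%.
- Beta(2,2), with s²=0.05: correlation 0.5/√0.35 = 0.85, z ≈ 2.96, about 84%.

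**4. Simulation.** Outcome = 0.30 × baseline + arm effect + noise, with no timing or content effect, 2,000 runs per setting, 110 per arm, no Hommel adjustment. Rejection rates of the pooled form:

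| Mean (SD) of P in Calm | Correlation with arm | d=0.45 | d=0.31 | d=0.20 | d=0 |
|---|---|---|---|---|---|
| 0.50 (0.15) | 0.92 | 0.889 | 0.5885 | 0.293 | 0.041 |
| 0.50 (0.29) | 0.78 | 0.7545 | 0.457 | 0.228 | 0.0485 |
| 0.50 (0.35) | 0.71 | 0.688 | 0.385 | 0.1855 | 0.0495 |
| 0.30 (0.23) | 0.68 | 0.6385 | 0.368 | 0.1845 | 0.0455 |
| 0.30 (0.32) | 0.55 | 0.4735 | 0.2545 | 0.1315 | 0.0455 |
| 0.15 (0.18) | 0.51 | 0.4125 | 0.247 | 0.134 | 0.0485 |
| 0.15 (0.25) | 0.39 | 0.242 | 0.1505 | 0.0865 | 0.0535 |
| 0.10 (0.17) | 0.38 | 0.2355 | 0.144 | 0.095 | 0.0525 |

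At week 20 (97 per arm, d=0.45) the range is 0.224-0.851. The Calm-only model, and the all-participant model with an arm term, reject in 4-6% in every setting. The d=0 column shows that the excess comes from the arm effect alone.

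**5. Collinearity as the reason for omitting arm.** If P is centred at the Calm mean and podcast is set to 0, its correlation with arm is exactly 0. With arm in the model, centring changes neither the timing coefficient nor its standard error. It makes the arm term readable and shows that arm can be kept.

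**The case against.** The strongest reply is that the article does not commit to the pooled form. The zero coding is never stated for these variables, the Calm-only form is one of the two being paralleled, and the absence of meditation records in the podcast arm could equally motivate a Calm-only analysis. This stands in part. The point is conditional on the pooled form being used, and a sound form is already listed. However, collinearity with arm is a difficulty only when both arms are in the model, so the stated reason points towards pooling. Nothing says which form to read if the two disagree.

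A reader might infer that the plan will usually report a spurious timing or content effect. The documents do not support that. They give no distribution for either proportion, the rate is below one half in several settings even at d=0.45 and in most at d=0.31, and it is nominal if Calm does nothing. Hommel adjustment would lower the rates by an unknown amount, though it would not change what the coefficient estimates. A claim that the pooled model would favour bedtime practice even where it is less helpful needs an assumed within-Calm slope for which the documents give no basis.

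It is also fair that the raw variables are correlated with arm as the article says, that the article already speaks of associations, and that these are supplementary analyses. Which form is used might be settled in an analysis plan that is not shown, but the article itself fixes the cross-reference and its rationale.

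**Conclusion.** The point holds in limited form. If the cross-reference is followed in its pooled form, the coefficient estimates mainly the Calm-versus-podcast difference and cannot isolate timing or content. When Calm works and neither feature matters, it is significant in roughly 24-89% of trials at d=0.45 and 14-59% at d=0.31, against about 5% when Calm has no effect. These figures rest on assumed Beta distributions, two-sided 0.05, complete cases and no multiplicity adjustment. The Calm-only form does not have the problem. The primary intent-to-treat comparison, the sample size and the data collection are untouched. It should be corrected because a wording change is enough, but it is not a threat to the trial's main conclusion.

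**What to change.** In Analytic Approach, state that the time-of-day and nonmeditative-content analyses use one of two models:

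- the Calm arm only, with outcome regressed on baseline and the exposure; or
- all participants, with outcome regressed on baseline, arm and the exposure centred at the Calm mean (0 for podcast), reading the centred term.

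State that the all-participant form with podcast coded 0 and no arm term will not be used, or at least not interpreted, as a timing or content effect. Remove collinearity as the reason for leaving arm out.

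The podcast app records its own session times, so a model with arm, own-session timing and their interaction is possible. It should be dropped or labelled exploratory, because session timing is chosen after randomization and a podcast session is not the counterpart of a meditation session.

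The cost is a few sentences and no new data. Apparent power will be lower than in the pooled test, because the information on timing and content comes only from the Calm arm.
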